### Intervention

The three intervention hospitals will participate in the five step implementation process described below. The control hospitals will receive a hard copy of the relevant NHFA guidelines. The evidence-based five step intervention within emergency departments to implement clinical pathways will be a combination of processes proposed by Doherty & Jones[14] and Kinsman et al.[7]. In brief, the three month implementation process entails:

#### 1. Engaging clinicians

The Chief Investigator will hold group discussions with emergency department medical and nursing staff regarding barriers and facilitators for clinical pathways whilst local clinicians will be recruited as Research Assistants. It is hoped that the employment of local clinicians will facilitate local opinion leadership.

#### 2. Clinical pathway development

Hospital-specific clinical pathways will be developed by Research Assistants in collaboration with clinicians at each emergency department. Pathway content will be consistent with NHFA and CSANZ guidelines for chest pain and AMI management, and will incorporate local resources and systems.

#### 3. Reminders

Reminder visits by the Chief Investigator will occur twice following implementation to liaise with clinical staff. Research Assistants will be tasked with reminding medical and nursing staff about the clinical pathway to promote utilisation.

#### 4. Education

The Research Assistant and Chief Investigator will facilitate education sessions during implementation to review evidence underpinning the clinical pathway and reinforce the role of the pathway itself. All staff will receive written material regarding thrombolytic drugs, including summaries of the national guidelines.

#### 5. Audit and feedback

Audit results reflecting compliance with the clinical pathway and thrombolysis administration will be communicated by the Chief Investigator to emergency department staff twice during the implementation of the clinical pathway. Participants will be encouraged to express their views on the advantages and pit-falls of the clinical pathway.

### Data Collection

Medical records will be identified by an International Classification of Diseases (ICD 10) report and audited using a specifically-designed data protocol. Initial data will include type of infarct, gender and age. Information regarding whether criteria were met for a thrombolytic drug will be checked. If criteria were met, then whether a thrombolytic was administered will be recorded, as will the time in minutes from presentation to administration. The level of adoption of the clinical pathway will be measured by identifying the presence of the pathway in audited records and by degree of documented completion of the pathway. A co-investigator will review 10% of the medical records to confirm accuracy of data extraction.

### Data Analysis

Use of thrombolytic drugs will be categorised as yes/no for each eligible patient, and intervention and control hospital groups will be compared at baseline and follow-up using a standard Chi-squared test. An independent sample *t*-test will be used to compare time to thrombolytic delivery between intervention and control groups at baseline and follow-up. Matched *t*-tests will assess differences between baseline and follow-up for both the intervention and control groups. Between-group comparisons allowing for the clustering of data will be undertaken. Documented usage of the clinical pathway will be measured by simple descriptive statistics such as percentage of AMI cases in which the pathway was used and proportion of the chart completed.

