**Methods/Design:**

The design is a two-arm, cluster-randomised trial with rural hospital emergency departments that treat and do not routinely transfer acute myocardial infarction patients. Six rural hospitals in the state of Victoria will participate, with three in the intervention group and three in the control group. Intervention hospitals will participate in a five-step clinical pathway implementation process: engagement of clinicians, pathway development according to local resources and systems, reminders, education, and audit and feedback. Hospitals in the control group will each receive a hard copy of Australian national guidelines for chest pain and acute myocardial infarction management. Each group will include 90 cases to give a power of 80% at 5% significance level for the two primary outcome measures: proportion of those eligible for thrombolysis receiving the drug and time to delivery of thrombolytic drug.

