### Study Design

A randomised controlled trial will be conducted involving six rural hospitals that treat and do not routinely transfer AMI patients. As displayed in table 1, pairs of hospitals were matched according to the anticipated number of eligible patients and on the basis of geographical separation in order to minimise the risk of a control hospital being influenced by procedures at an intervention hospital. Randomisation within pairs to either the intervention (n = 3) or control (n = 3) groups occurred by a simple coin toss.

**Table 1 T1:** Geographic characteristics and anticipated number of patients per site.

	**Kilometres between matched hospitals^a^**	**Mean number of eligible patients per year^b^**
Intervention Control	318	60 55

Intervention Control	463	50 50

Intervention Control	155	15 20

^a ^Source: Google Earth

^b ^Estimates based on previous research [7]

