### Sample size

A 20 minute reduction in time to thrombolytic administration represents a modest improvement[7]. A total post intervention sample size of 90 patients is required to detect a 20 minute reduction in thrombolytic delivery time and a 10% improvement in eligible patients receiving thrombolysis (significance level of 5%, power of 0.8, and intra-cluster correlation coefficient of 0.283)[13]. Based on anticipated total attendance rates (i.e. 125 eligible case per annum in each condition) there will be nine months of pre and nine months of post intervention data collected.

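### Patient-level chi-squared and t-tests are named for both primary outcomes of a six-hospital cluster trial, and the plan does not say that the promised cluster-adjusted comparison overrides them

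*Protocol article*

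**What the plan says.** Under Study Design the hospital is the unit of allocation: "Randomisation within pairs to either the intervention (n = 3) or control (n = 3) groups occurred by a simple coin toss". Under Sample size the calculation rests on "significance level of 5%, power of 0.8, and intra-cluster correlation coefficient of 0.283". The abstract names two primary outcomes, the proportion of eligible patients given the drug and the time to its delivery.

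For the first, the Data Analysis section says "intervention and control hospital groups will be compared at baseline and follow-up using a standard Chi-squared test". For the second, an independent-samples t-test "will be used to compare time to thrombolytic delivery between intervention and control groups at baseline and follow-up". Two sentences later it adds "Between-group comparisons allowing for the clustering of data will be undertaken". That sentence does not say that it supersedes the two named tests, or which result is the trial's answer if they differ.

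**The concern.** A standard chi-squared test and an independent-samples t-test take their standard errors from the number of patients. Here the independent units are six hospitals, and patients within a hospital resemble one another. An ICC of 0.283, which the protocol itself uses, means that more than a quarter of the outcome variance lies between hospitals. Chance differences between two sets of three hospitals can then pass for a treatment effect.

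This is more than a detail left for later. The protocol names the tests, so a later analysis plan would have to overrule the text, not just complete it. As written, each primary outcome can yield two p-values, one of them invalid, with no rule for choosing. The invalid tests are also the only between-arm tests named specifically enough to run from the article.

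**Working it through.** **Inputs from the protocol.** Three hospitals per arm (Study Design); ICC 0.283 and alpha 5%, taken as two-sided (Sample size). Expected eligible patients per year are 60, 50, 15 against 55, 50, 20 (Table 1), that is 125 per arm. Nine months gives 125 × 9/12 = 93.75 per arm, which agrees with the abstract's 90 per group.

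**Assumptions.** The single ICC applies to both outcomes; the protocol does not say which one it belongs to. Matching explains none of the variation between hospitals. About two-thirds of eligible patients are treated, taken from the Background's statement that up to one-third are not.

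**Formula.** With m patients per hospital the variance of the arm difference is inflated by DE = 1 + (m − 1) × ICC. A test that ignores this has true type I error of about 2 × [1 − Φ(1.96/√DE)]. With ICC = 0, DE = 1 and the formula returns the nominal 5%. For unequal hospitals m is replaced by Σm²/Σm. At nine months this is 37.95 in one arm and 35.55 in the other, mean 36.75.

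**Results at ICC 0.283.** The simulated column gives null trials with beta-binomial data for the chi-squared test and normal random-intercept data for the t-test.

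| Setting | DE | Formula | Simulated |
|---|---|---|---|
| 90 per group, 30 per hospital | 1 + 29 × 0.283 = 9.21 | 52% | 53-54% |
| Table 1 sizes, nine months | 1 + 35.75 × 0.283 = 11.12 | 56% | 57-58% |
| 90 in total, 15 per hospital | 1 + 14 × 0.283 = 4.96 | 38% | 40-41% |
| Time, two-thirds treated, 20 per hospital | 1 + 19 × 0.283 = 6.38 | 44% | about 46% |
| Time, two-thirds treated, Table 1 sizes | 1 + 23.5 × 0.283 = 7.65 | 48% | about 50% |

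The third row is there because the Sample size section reads "A total post intervention sample size of 90 patients is required to detect a 20 minute reduction in thrombolytic delivery time", whereas the abstract reads "Each group will include 90 cases to give a power of 80% at 5% significance level for the two primary outcome measures". The last two rows are there because time to delivery exists only for patients who received the drug.

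**Smaller ICCs, at about 90 per group.**
- ICC 0.05: DE = 1 + 29 × 0.05 = 2.45 gives 21%. Table 1 sizes give DE 2.79 and 24% (simulated about 24%).
- ICC 0.02: DE = 1.58 gives 12%. Table 1 sizes give DE 1.715 and 13% (simulated about 14%).
- With 90 in total (m = 15) the same two ICCs give DE 1.70 and 13%, and DE 1.28 and 8%.

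**A valid comparator.** A two-sample t-test on the six hospital summaries (4 df, critical value 2.776) rejects in about 5-6% of the same null trials at ICC 0.283.

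**Its power.** For 67% versus 77% treated at 90 per arm, the standard error is √[(0.667 × 0.333 + 0.767 × 0.233) × 9.21/90] = 0.203. The non-centrality is 0.10/0.203 = 0.49, and power on 4 df is about 7%.

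**The case against.** The strongest reply is that the plan does not ignore clustering. It commits without qualification to cluster-adjusted between-group comparisons, builds an ICC into its sample size and argues in the Discussion for cluster randomisation. A condensed article may leave the model and its small-sample correction to an analysis plan. All of that stands. A reader might infer that clustering is neglected altogether, and the text does not support that. Nor is the missing name of a clustering method a finding here. What remains is that the named tests are wrong for this design and nothing demotes them.

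A second reply concerns the size. It is tempting to say that both tests reject a true null more than half the time. That holds only at about 90 per group with all eligible patients counted. It fails for time to delivery if a third of patients are untreated, and for both outcomes if 90 is the total. Matching that explained variation between hospitals would lower every figure. The protocol matched on expected patient numbers and geographical separation, and gives no data on how far either predicts the outcomes.

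A reader might also infer that a significant result would mostly reflect differences between hospitals. A type I error rate does not show that; it depends also on the true effect and how plausible it was beforehand.

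Finally, the valid test has very little power. This is true, but it is a property of six hospitals at this ICC, and an invalid test does not add information.

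**Conclusion.** The point holds in this form: the plan names patient-level tests for both primary outcomes of a hospital-randomised trial, also promises cluster-adjusted comparisons, and does not say which governs. At the protocol's own ICC the named tests have a true error rate of roughly 40-58%, depending on whether 90 is per group or in total and on how many patients contribute a delivery time. The per-group reading has better support, from the abstract and from the expected 125 cases a year per arm. The range rests on using one ICC for both outcomes, on no gain from matching and, for time, on two-thirds being treated. The conclusion does not depend on the exact figure: at about 90 per group the error is still about 21-25% at ICC 0.05 and 12-14% at ICC 0.02. The text is wrong as written and should be corrected before analysis.

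**What to change.** State in the Data Analysis section that the cluster-respecting comparison is the primary analysis of each primary outcome, with the hospital as the unit. Two options would serve:

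- six hospital summaries (proportions, or mean or log times) compared with t on 4 df; or
- a patient-level model with a small-sample correction suited to the outcome type. A correction made for linear mixed models does not carry over directly to the yes/no outcome.

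Say also whether the matched pairs enter the primary analysis. A paired analysis of three pairs has 2 df and a critical value of 4.303 against 2.776, so keeping the pairs for a sensitivity analysis is defensible if stated in advance. Report the patient-level chi-squared and t-test comparisons descriptively, without p-values.

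The change is one of wording and needs no new data. The price is wider confidence intervals and an open statement that power is low, about 7% for 67% versus 77% treated at 90 per group. That limitation comes from the design and should be reported as such.

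### The matched t-tests of baseline against follow-up have no patient pairs, and a within-arm change does not estimate the pathway effect

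*Protocol article*

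**What the plan says.** The Sample size section says that "there will be nine months of pre and nine months of post intervention data collected". Data Collection says how cases enter: "Medical records will be identified by an International Classification of Diseases (ICD 10) report". For each eligible case the audit records whether the drug was given and, if so, "the time in minutes from presentation to administration". Nothing in the article follows a patient from one period to the next or links a baseline case to a follow-up case.

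Data Analysis takes the patient as the unit for the first outcome ("Use of thrombolytic drugs will be categorised as yes/no for each eligible patient") and compares the arms by chi-squared test at each period. For the second outcome, "An independent sample *t*-test will be used to compare time to thrombolytic delivery between intervention and control groups at baseline and follow-up". Then comes the sentence at issue: "Matched *t*-tests will assess differences between baseline and follow-up for both the intervention and control groups". It does not name the pairing unit or the outcome. The next sentence adds between-group comparisons that allow for clustering, without naming a method.

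Under Study Design, the hospital is the randomised unit: "Randomisation within pairs to either the intervention (n = 3) or control (n = 3) groups occurred by a simple coin toss". Objective 2 in the Objectives section is to measure the effect of the intervention on the two outcomes.

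**The concern.** A matched t-test needs observations that belong together in pairs. Patients admitted in one nine-month window have no counterparts in a later window, so the named test does not fit patient-level data. Read at hospital level it is a real pairing, but a very small one, and the text does not say that it is intended.

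The second problem holds under both readings. Testing each arm against its own baseline does not compare the arms. Care may improve in all six hospitals over the study for reasons unrelated to the pathway, and the control hospitals also receive the guidelines. A significant change in the intervention arm is then compatible with no pathway effect, and so is a significant change in that arm beside a non-significant one in the control arm. The matched tests are the only analysis in the article that explicitly addresses change from baseline, and nothing labels them descriptive. They could therefore be read as evidence of effect.

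**Working it through.** **1. Are there patient pairs?** Sample size sets two separate periods, Data Collection gives one result per audited case, and no section links cases across periods. There are none.

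The two sets need not be equal in number either. Sample size anticipates 125 eligible cases a year per arm, so nine months gives 125 × 0.75 = 93.75. A time exists only for treated cases. Assume 67% are treated at baseline (from the Background's statement that up to one-third are not) and 77% at follow-up (reading the 10% improvement as absolute):

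- baseline: 93.75 × 0.67 ≈ 63 times
- follow-up: 93.75 × 0.77 ≈ 72 times

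If the pathway works as hoped, the counts are expected to differ.

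**2. What does pairing by hospital give?** There are three hospitals per arm, hence three differences, 3 − 1 = 2 df, and a two-sided 5% critical t of 4.30.

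Power for a 20-minute change can be shown only as a range. The ICC of 0.283 is from the Sample size section. The total SD and the correlation r of a hospital's level between periods are assumptions. Cases per hospital per period are set at m = 90/3 = 30 for simplicity, although Table 1 anticipates unequal hospitals.

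- SD of a hospital difference = √[2 × 0.283 × SD² × (1 − r) + 2 × 0.717 × SD² / 30]
- noncentrality = 20 × √3 / (SD of difference)

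| Assumed SD (min) | Assumed r | SD of difference | Power |
|---|---|---|---|
| 30 | 1.0 | 6.6 | 76% |
| 40 | 0.8 | 16.0 | 24% |
| 50 | 0.5 | 28.8 | 12% |

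Over SDs of 30 to 50 minutes and r of 0.5 to 1.0, power runs from 12% to 76%.

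**3. What does a within-arm test show when the pathway does nothing?** Suppose both arms improve by the same amount. Take 90 different patients per period in an arm, an assumed SD of 40 minutes, an unpaired t-test with 178 df, and no allowance for clustering. The standard error is 40 × √(2/90) = 5.96 minutes. Let p be the chance that the within-arm test is significant. With independent arms, the pattern of significance in the intervention arm only has probability p(1 − p).

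| Assumed shared fall (min) | p | p(1 − p) |
|---|---|---|
| 5 | 13% | 12% |
| 10 | 39% | 24% |
| 20 | 92% | 8% |

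In general p(1 − p) is 0.8 × 0.2 = 16% at p = 0.8 and 0.5 × 0.5 = 25% at p = 0.5. A valid two-sided 5% test between arms would wrongly favour the intervention 2.5% of the time. With no trend, the chance of a significant improvement in the intervention arm and none in the control arm is 0.025 × 0.975 = 2.4%, so the excess comes entirely from the assumed trend.

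**4. What else is planned?** Between-arm tests at baseline, between-arm tests at follow-up, and clustered between-group comparisons of unstated form. A group-by-period contrast or a follow-up difference adjusted for baseline is not named.

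**The case against.** The strongest reply is that the matched tests are a side analysis. The section keeps the randomised comparison: it tests between arms at follow-up for both outcomes and adds comparisons that allow for clustering. It nowhere says that the conclusion rests on the within-arm tests. Within-arm change could also serve Objective 1, hospital performance against recommendations. All of this stands, and it limits the point to one planned test.

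A second reply is that pairing hospital means is legitimate, since the hospital is the randomised unit and each contributes both periods, and that a condensed article may leave the pairing unit to a fuller document. The first half stands: 2 df means low power, not an invalid test. The second helps less. The surrounding sentences describe patient-level tests, and this one would be taken the same way. The hospital reading also leaves the time-trend problem untouched.

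A reader might infer that arbitrary pairing makes the standard errors meaningless. It does not. For independent observations the expected covariance within arbitrary pairs is zero, so the paired standard error still targets the right variance. With 90 pairs the loss is degrees of freedom (89 instead of 178), any cases left unpaired, and reproducibility, because the result depends on the pairing chosen. Ignored clustering is a separate fault.

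Finally, a between-arm comparison of change is not the only valid analysis. Randomisation also supports a comparison at follow-up, with or without baseline adjustment.

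**Conclusion.** The sentence is wrong as written. It names a test for which the data hold no patient pairs, does not state the one pairing that exists, and addresses change in a way that cannot answer Objective 2. This rests on the article's own description of the two audits and needs no assumed figure. It should be fixed before analysis, but it does not undermine the trial's randomised comparison.

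The numerical size is illustrative only. The 12% to 76% power range depends on assumed SDs and period correlations. The p(1 − p) figures depend on a shared trend that the article does not give, and on a reader treating significance in one arm only as proof of effect, a rule the article does not state. A reader might infer that the plan discards its control group, or that the trial runs a 16% or 25% false-positive rate. The article supports neither. The gap is narrower: no between-arm comparison that uses the baseline data is named.

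**What to change.** Replace the matched t-test sentence. Report each arm's baseline value, follow-up value and change descriptively, by hospital, with intervals that respect hospital clustering, and state that no claim of effect rests on them. Base the conclusion on the clustered between-arm comparison already foreseen, now specified to use the baseline data: either a group-by-period contrast or a follow-up difference adjusted for baseline, with the hospital as the unit and small-sample degrees of freedom.

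The cost is a rewritten sentence or two in Data Analysis and no new data. The downside is precision. A contrast of change has 3 − 1 = 2 df if the matched pairs are kept (critical t 4.30), or about 3 + 3 − 2 = 4 df if they are ignored (critical t 2.78). Intervals will therefore be wide. That limit comes from having six hospitals, and the matched t-tests do not avoid it.

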## Discussion

The evidence for clinical pathways remains inconclusive and the reasons for the variable results reported may relate to both implementation strategies and research designs. It is important to determine rigorously whether clinical pathways have an integral role to play in enhancing compliance with evidence-based practice. Randomisation of individual patients within a single ward or hospital to complex interventions such as clinical pathways will lead to contamination of comparable samples and a high risk of bias. In these situations a cluster randomised controlled trial is a preferred method to minimise the influence an intervention may have on clinical practice in control groups.

This study will contribute to the knowledge base on what is required to translate evidence into practice in rural settings. In this study improved compliance with thrombolytic guidelines via clinical pathways will increase AMI survival rates in rural hospitals and help reduce rural-urban mortality inequalities. Such translation science will have the potential to be applied in a range of clinical settings for many different conditions.
